## Abstract

**Background::**

Though several neuroprotective agents have been evaluated as potential treatments for acute ischemic stroke, none have demonstrated a definitive treatment efficacy, which remains elusive. HT047 is an herbal extract of *Scutellaria baicalensis* and *Pueraria lobata*, both of which have been widely used to treat ischemic stroke in traditional Korean medicine. The aims of this trial are to investigate whether HT047 can improve neurologic status, particularly motor function, in acute ischemic stroke patients, and to determine the safety of HT047.

**Methods::**

A multicenter, double-blind, randomized, placebo-controlled, 3-arm parallel group, phase II trial will be conducted in patients who have had an acute ischemic stroke within the past 14 days. The participating patients must have a Fugl-Meyer assessment (FMA) motor score ≤55, with arm or leg weakness, and Korean version of the National Institutes of Health Stroke scale (K-NIHSS) score of ≥4 and ≤15. Seventy-eight participants will be randomized in a 1:1:1 ratio and given high-dose HT047 (750 mg 3 times a day), low-dose HT047 (500 mg 3 times a day), or a placebo for 12 weeks. The primary endpoint is the change in FMA motor score between baseline and week 12. Secondary endpoints are as follows: the change in FMA motor score at weeks 4 and 8 from baseline; the change in FMA motor score at weeks 4, 8, and 12 from baseline according to the timing of treatment initiation (either within 1 week, or 1–2 weeks), or according to the presence of prognostic risk factors (hypertension, diabetes, dyslipidemia, etc); the change in K-NIHSS and Korean versions of the modified Rankin scale (K-mRS) and the modified Barthel index at weeks 4 and 12 from baseline; and the proportion of subjects at week 12 with a K-NIHSS score of 0 to 2, or with K-mRS scores of 0, ≤1, and ≤2.

**Discussion::**

This study is a 1st-in-human trial of HT047 to explore the efficacy and safety in acute ischemic stroke patients. The results will provide the appropriate dosage and evidence of therapeutic benefit of HT047 for stroke recovery.

**Trial registration::**

ClinicalTrials.gov (NCT02828540) Registered July 11, 2016.

## Introduction

1

Ischemic stroke remains a leading cause of death and serious long-term disability worldwide. Intravenous thrombolysis and endovascular treatment have proven to be the most effective treatments for acute ischemic stroke. However, because of the narrow time window available for these treatments, only a minority of patients receive these treatments, warranting the need for alternative therapeutic approaches.

Despite the failure of several clinical trials, neuroprotection remains a promising alternative or adjunct treatment of acute stroke.^[1]^ Recent advances have revealed that the induction of endogenous neurorestorative processes in the brain, including neurogenesis, synaptogenesis, vascular and axonal remodeling, and oligodendrogenesis aid in neurologic recovery during the subacute and chronic phases.^[2]^ Neurorestoration has increasingly become an important therapeutic approach, which offers a substantially longer therapeutic time window than the limited time window available for drugs with neuroprotective properties, because neurons in the ischemic penumbra only survive temporarily.^[1]^ To facilitate an optimal functional recovery after ischemic stroke, attempts have been recently made to develop drugs with both neuroprotective and neurorestorative properties.^[3–5]^ In this regard, many natural products have been reported to possess both of these properties as they contain a wide range of bioactive compounds.^[6]^

The HT047 is a multiherbal extract of the roots of *Pueraria lobata* and *Scutellaria baicalensis*. It was developed by screening more than 200 herbs used in traditional Korean medicine for the treatment of stroke, with the aim of promoting both neuroprotection and neurorestoration following ischemic stroke. *P lobata*, *S baicalensis*, and their major active compounds, which include puerarin, daidzin, and daidzein in *P lobata*, and baicalin, baicalein, and wogonin in *S baicalensis*, are well known for their neuroprotective effects against cerebral ischemia.^[7–10]^ Moreover, previous studies have shown that the major active compounds of HT047 (puerarin, daidzein, baicalin, baicalein, and wogonin) stimulate key restorative processes, including angiogenesis, neurogenesis, axonal sprouting, dendritic branching, and synaptogenesis.^[11–18]^ Based on these preclinical findings, we designed this study protocol to test the efficacy and safety of 12-week treatment with HT047 in acute ischemic stroke patients with motor deficits.

### Objectives

1.1

The primary objective is to examine the efficacy of HT047 for the recovery of motor function in patients with acute ischemic stroke. The secondary objectives are to investigate whether HT047 enhances neurologic recovery and to evaluate the safety of HT047. The exploratory objective is to assess the efficacy of HT047 on cognitive function.

### Design

1.2

This study is a phase 2, multicenter, double-blind, randomized, placebo-controlled, superiority trial with 3 parallel groups. Eligible participants will be randomly assigned to 1 of 3 groups: HT047 high- or low-dose, or placebo with a 1:1:1 allocation ratio, and will receive the investigational product for 12 weeks.

## Methods

2

### Study setting

2.1

The participants will be recruited from eight institutes in the Republic of Korea, including the Departments of Neurology at Kyung Hee University Hospital (Seoul), Kyung Hee University Hospital at Gangdong (Seoul), Hanyang University Hospital (Seoul), Hanyang University Guri Hospital (Gyeonggi-do), Hanyang University Myongji Hospital (Gyeonggi-do), Gachon University Gil Medical Center (Incheon), Hallym University Dongtan Sacred Heart Hospital (Gyeonggi-do), and Chosun University Hospital (Gwangju). Regular investigators’ meetings will be held to encourage enrollment and regular newsletters will be sent until the required sample size is reached. The 1st patient was enrolled in August 4, 2016.

### Eligibility criteria

2.2

The inclusion and exclusion criteria are provided in Table 1. Briefly, patients are eligible if they have had an ischemic stroke confirmed by brain imaging within 14 days of screening, are aged 19 years or older, have arm or leg weakness with a Fugl-Meyer assessment (FMA) motor score ≤55 at screening, and have a Korean version of the National Institutes of Health Stroke scale (K-NIHSS) score ≥4 and ≤15 at screening.

**Table 1 T1:**
[figure not shown]
Inclusion and exclusion criteria.

### Procedures

2.3

This study is designed to initiate treatment with high- or low-dose HT047 or placebo in subjects with acute ischemic stroke within 2 weeks of the onset of disease and evaluate neurologic and functional recoveries during 12 weeks of treatment in these subjects. The schedule for enrollment, interventions, and assessment of this study is shown in Table 2. The investigator will obtain written informed consent from subjects who voluntarily agreed to participate in the study before eligibility assessment. During the study treatment period, participants will visit the hospital at weeks 1, 4, 8, and 12. Since this is a 1st-in-human trial for HT047, subjects will have a study visit at week 1 to undergo laboratory tests, electrocardiogram, and chest X-ray, also, the subject's physical status will be examined before he/she is sent home. Neurologic function assessments will be carried out at subsequent visits. At week 12, the subject will again undergo laboratory tests, electrocardiogram, and chest X-ray and overall changes in the subject's status will be confirmed before all study procedures are ended.

**Table 2 T2:**
[figure not shown]
Study schedules.

### Interventions

2.4

The HT047 will be produced by Bioland Co, Ltd, a bulk Good Manufacturing Practice-certified manufacturer (Osong, Chungcheongbuk-do, Republic of Korea). The dried roots of *P lobata* and *S baicalensis* will be mixed together in an 8.0:1.1 weight ratio and then be extracted twice with 30% ethanol in distilled water for 3 hours at 70°C. The liquid extract will be filtered, concentrated under 60°C, and vacuum dried to yield the extract, HT047. The study drug (a tablet containing 250 mg of HT047) and a placebo, identical in appearance to the study drug, will be provided by Kolmar Korea Inc (Sejong-si, Republic of Korea).

Participants will receive either the investigational product (HT047) or placebo 3 times a day for 12 weeks, starting from the morning after the baseline visit. Three tablets will be administered per dose as follows: 3 HT047 tablets for high-dose group (2250 mg/d), 2 HT047 tablets, and 1 placebo tablet for low-dose group (1500 mg), and three placebo tablets for placebo group. A one-month supply of the investigational products will be given to the subjects at baseline and weeks 4 and 8. At each visit, subjects will be asked to return the remaining investigational products for calculating their compliance and will be encouraged to adhere to the prescribed dosage regimen.

Physiotherapy sessions will be freely prescribed by the patient's attending physician, neurologist, or rehabilitation physician, according to medical opinion and subjects’ requests. Subjects will be prohibited from concomitant use of any medications which can induce hepatotoxicity, such as propylthiouracil, ketoconazole, isoniazid, valproate, and phenytoin; any medications containing *P lobata*, *S baicalensis*, or their major components (puerarin and baicalin, respectively); selective serotonin reuptake inhibitors; amphetamine; cholinesterase inhibitors, such as donepezil, rivastigmine, and galantamine; memantine; nootropics, such as choline alfoscerate, acetyl-l-carnitine, oxiracetam, and *Ginkgo biloba.*

The allocated intervention will be discontinued if a participant or a participant's legal representative wishes to discontinue study participation or if the investigator decides to discontinue due to medical or administrative reasons (adverse events, continuous protocol violations, etc).

### Randomization and blinding

2.5

Eligible participants will be randomly assigned to one of the following 3 groups in a 1:1:1 ratio: high-dose (750 mg 3 times a day), low-dose (500 mg 3 times a day), and placebo groups. An independent statistician will generate a list of random numbers using a centralized stratified block randomization method. Randomization will be stratified according to the hospital, so that all hospitals have a 1:1:1 ratio. The study drug and placebo will be sealed in sequentially numbered identical bottles according to the allocation sequence. Each participant will be assigned an order number and will receive the investigational product or placebo in the corresponding prepacked bottles. Participants and all research personnel will be blinded to the assignment. The randomization code will be kept secure by an independent statistician and can only be broken in the case of an emergency. If a code break occurs, the investigator will report the reason and procedures and the administration of investigational drug will be discontinued.

### Outcome measures and endpoints

2.6

The Korean version of the FMA motor score will be used to measure the primary endpoint.^[19]^ The motor domain of FMA ranges from a score of 0 (flaccid hemiplegia) to 100 (normal movement), with 66 points for the upper limb and 34 points for the lower limb. An educated physiotherapist will perform all motor assessments at baseline and weeks 4, 8, and 12. The K-NIHSS and Korean versions of the modified Rankin scale (K-mRS), the modified Barthel index (K-mBI), and the montreal cognitive assessment (MoCA-K) will be used at baseline and weeks 4 and 12.

The primary efficacy endpoint is the change in FMA motor score at week 12 from the baseline. The secondary efficacy endpoints are: the change in FMA motor score at weeks 4 and 8 from the baseline; the change in FMA motor score at weeks 4, 8, and 12 from baseline according to the timing of treatment initiation after the onset of stroke (either within 1 week or 1–2 weeks) or according to the presence of prognostic risk factors (hypertension, diabetes, dyslipidemia, etc); the change in K-NIHSS and K-mRS scores at weeks 4 and 12 from the baseline; the proportion of subjects with a K-NIHSS score of 0 to 2 at week 12; the proportion of subjects with a K-mRS score of 0, ≤1, and ≤2 at week 12; and the change in K-MBI score at weeks 4 and 12 from the baseline. Exploratory endpoint is the change in MoCA-K score at week 12 from baseline.

Safety endpoints are the adverse events, significant changes in vital signs and physical examination; and abnormal laboratory tests, electrocardiogram, and chest radiography results. Laboratory tests will include hematology, electrolyte, blood chemistry, lipid battery, blood coagulation, and urinalysis.

### Sample size

2.7

The primary endpoint of the study is the change in FMA motor score at baseline from that after 12 weeks. A sample size of 22 in each group will be sufficient to detect a clinically important difference of 14.5 points on the FMA score, assuming a standard deviation (SD) of 19.2. This estimate is based on the findings of the fluoxetine in motor recovery of patients with acute ischemic stroke trial, which reported a difference of mean ± SD 90-day FMA score change between fluoxetine group (n = 57, 36.4 ± 21.3) and control group (n = 56, 21.9 ± 16.7).^[20]^

Because this HT047 trial is a phase 2 exploratory clinical trial for appropriate dose selection, we did not consider adjustment to control for type 1 errors resulting from the comparison between the 3 groups. However, in the comparison of primary efficacy outcome between the 3 groups, multiple comparisons will be performed to control for the experiment-wise error rate. We will use a Student *t* test of the difference between mean values, a power of 80%, and a significance level of 10%. With a 15% anticipated drop-out rate considered, we plan to enroll 26 patients per group (a total of 78 patients).

The formula for the sample size for comparison of 2 mean values is as follows:
 
[figure not shown]

where *Z*_*α*/2_ is the normal distribution threshold of type 1 error (*α* = 0.10/2), *Z*_1-*β*_ is the normal distribution threshold of power (1 − β = 0.8), *μ*_*T*_ is the mean change of 12-week FMA score in HT047 group (high dose or low dose), *μ*_*C*_ is the mean change of 12-week FMA motor score in control group, and σ is the standard deviation.

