### Statistical analysis

2.8

Efficacy will be assessed in the full analysis set (FAS) and the per-protocol (PP) set. The FAS will include all subjects who meet the inclusion/exclusion criteria, provide voluntary informed consent to participate in the study, receive at least 1 dose of the investigational product after randomization, have FMA assessment, that is, the primary efficacy endpoint, at screening, and at least once at weeks 4, 8, or 12 during the follow-up period. The PP set will include all FAS subjects who do not have any major violations such as major protocol violations (excluding minor violations) and have a primary efficacy assessment per protocol. Subjects with an overall medication compliance of <70% will be excluded from the PP set. Safety will be assessed in the safety set, which will comprise of all subjects who receive at least 1 dose of the investigational product after randomization.

The primary efficacy endpoint will be analyzed both in the FAS and the PP sets. The final conclusions of the study will be made based on the FAS results, in principle. Mean, SD, median, and range (minimum, maximum) of FMA motor score before dosing and 12 weeks after dosing, as well as score change between the 2 time points, will be presented for the high- and low-dose HT047, and the placebo groups. To assess intergroup differences in the primary endpoint, that is, FMA change, analysis of covariance, with baseline FMA as a covariate, and Tukey multiple comparison test will be carried out. Dunnett multiple comparison, which would consider the placebo group as a comparator group, will not be used because this phase 2 study aims to evaluate adequate dosage and therefore, will compare the HT047 high-dose group with the HT047 low-dose group.

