A comprehensive statistical analysis plan will be finalized prior to database locking. Details of statistical analyses that are not presented in the protocol will be described in the statistical analysis plan. All statistical analyses will be performed at a 2-sided significance level of 10%. To handle the missing data, the last observation carried forward method will be used for FMA motor score, the primary outcome variable. If FMA motor score is measured only at screening, substitution for missing data will not be performed. Similarly, for the other outcome variables, missing data will not be substituted and included in the statistical analysis. Interim analysis will not be performed.

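### The 80% power in section 2.7 describes one unadjusted t test; under the planned Tukey comparison it is about 66% per dose with 22 per arm

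*Protocol article*

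**What the plan says.** Section 2.7 (Sample size) states that 22 patients per group are "sufficient to detect a clinically important difference of 14.5 points on the FMA score", with an SD of 19.2. The basis is a Student t test comparing two means, with "a power of 80%, and a significance level of 10"%. The formula compares one HT047 dose with control and uses the normal quantile for a type 1 error of 0.10/2. Allowing for 15% drop-out, enrolment is 26 per group, 78 in total.

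On multiplicity, the same section first says that, as this is an exploratory phase 2 trial, "we did not consider adjustment to control for type 1 errors resulting from the comparison between the 3 groups". It then turns with a 'However' to the comparison of the primary outcome, where "multiple comparisons will be performed to control for the experiment-wise error rate".

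Section 2.8 (Statistical analysis) names the method: "analysis of covariance, with baseline FMA as a covariate, and Tukey multiple comparison test will be carried out". It rejects Dunnett because the two doses are also to be compared with each other. It also sets the level: "All statistical analyses will be performed at a 2-sided significance level of 10"%. No power is given for the Tukey comparison.

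**The concern.** The article states both a power and a primary test, and they do not belong together. The 80% is for a single pairwise t test at 10%. The primary analysis holds the 10% over three pairs, so each pair faces a higher critical value. Someone who reads that 22 per group is enough for 14.5 points will take the chance of missing that effect in a given dose-versus-placebo comparison to be 20%. Under the planned test, with 22 per arm and no gain from the covariate, it is about 34%.

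What is at stake is how a negative result is read. The trial is meant to guide dose choice and a phase 3 trial, and a non-significant dose could be discounted on the strength of a power it never had. There is no added false-positive risk: the Tukey procedure protects the experiment-wise error.

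**Working it through.** **Inputs.** Difference 14.5 points, SD 19.2, two-sided alpha 0.10, power 0.80, 22 evaluable and 26 enrolled per arm, 15% drop-out (section 2.7). Three arms at 1:1:1 (section 1.2). ANCOVA with Tukey, all analyses at two-sided 10% (section 2.8). No single sentence ties the 10% to Tukey. It follows from the experiment-wise commitment in 2.7, the named method in 2.8 and the general level in 2.8, and no other level is given.

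**The plan's own figures.**
- SD: √[(56 × 21.3² + 55 × 16.7²)/111] = 19.16, which rounds to 19.2.
- n = 2 × 19.2² × (1.645 + 0.842)² / 14.5² = 21.7, so 22 per arm.
- Drop-out: 22/0.85 = 25.9, so 26 per arm and 78 in total.
- Standard error of a difference at 22 per arm: 19.2 × √(2/22) = 5.79. Noncentrality: 14.5/5.79 = 2.50.
- Power of the unadjusted test: 80.5% by the normal approximation, 79.4% by the noncentral t with 42 df.

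The stated sample size therefore reproduces.

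**The same inputs under Tukey.** The critical |t| for a pair is q(0.90; 3 groups, df)/√2. Power comes from the noncentral t with the noncentrality above. Using 62 df or 63 df (with or without one covariate) makes no visible difference.

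| Evaluable per arm | Critical \|t\| | Noncentrality | Power per dose vs placebo |
|---|---|---|---|
| 22 | 2.09 (per-pair two-sided alpha about 0.041) | 2.50 | 66.1% |
| 26 | 2.08 | 2.72 | 73.8% |

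A simulation with 200,000 replicates at 22 per arm also gives 66%. At 22 per arm, 80% power per comparison is reached at a true difference of about 17.0 points.

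**What the adjustment does.** In the simulation, leaving all three pairs at an unadjusted 10% gives an experiment-wise error of about 22%. Tukey brings it back to about 10%, and the lower power per pair is the price.

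**Power over both doses (simulation, 22 per arm).**

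| True effects | At least one dose beats placebo | Both do |
|---|---|---|
| Both doses 14.5 points | 81% | 51% |
| One dose 14.5, the other 0 | 68% | 2% |

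The 2% in the last cell includes a false positive for the inactive dose.

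**Credit for the baseline covariate.** With correlation r between baseline and change, the residual SD is 19.2 × √(1 − r²). The article states no r, so these values are assumptions.

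| r | 22 per arm | 26 per arm |
|---|---|---|
| 0 | 66% | 74% |
| 0.3 | 70% | 78% |
| 0.4 | 74% | 81% |
| 0.5 | 79% | 85% |

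**The case against.** The strongest defence is that nothing is hidden or miscalculated. Section 2.7 says that the sizing is unadjusted, gives the exploratory phase 2 reason, and then says that the analysis will be adjusted. A reader might infer that these two sentences contradict each other. They do not: the natural reading of the 'However' is unadjusted sizing followed by adjusted analysis. A reader might also infer an arithmetic error, but 22 and 26 reproduce exactly. Both parts of this defence stand. What they leave open is that the article discloses the choice without saying that power falls, and the only power it gives is for a different test.

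Second, 66% is close to the least favourable case. The full analysis set needs only one follow-up FMA assessment and carries the last value forward, so more than 22 per arm may be analysed, although carried-forward values may dilute the effect. The covariate may also recover power: with all 26 per arm and r of about 0.4, 80% is reached. This stands as a possibility, which is why a range is shown. But the article assumes no correlation, and entry at FMA ≤55 narrows the baseline range by an amount that cannot be quantified here.

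Third, if both doses work, the chance that at least one beats placebo is about 81%. That is correct, and quoting the 51% for both doses alone would be one-sided. It does not rescue the stated figure, which is defined for one dose against control, and it drops to 68% if only one dose works.

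Two further readings go too far. One might say that an observed difference below about 12.1 points (2.09 × 5.79) cannot be significant. That holds only for 22 per arm and a residual SD of exactly 19.2; at 26 per arm the threshold is about 11.1. One might also ask for a different multiple-comparison procedure, but the article gives a reason for Tukey, enrolment has begun, and a closed F-test procedure would still fall short of 80% at 22 per arm (about 69-75%).

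**Conclusion.** The point holds as a mismatch between the stated power and the planned test. The 80% is right for one unadjusted dose-versus-placebo t test at two-sided 10%. It is not the power of the primary analysis as planned, which is about 14 points lower with 22 per arm (66%) and about 6 points lower with 26 (74%). These figures rest on the plan's difference and SD, on a 10% experiment-wise level inferred from sections 2.7 and 2.8 together, and on no gain from baseline adjustment. Under favourable but unstated assumptions about retention and correlation, 80% could be reached. The documents do not support calling this a calculation error, an internal contradiction or a threat to type 1 error control.

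**What to change.** In section 2.7, keep the sentence on unadjusted sizing, since it is the only statement of how multiplicity was handled in setting the sample size. Reword it to say that it concerns the sample size only and that the 80% refers to one unadjusted pairwise comparison. Then add:

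> Under the planned Tukey comparison at 10% experiment-wise, power per dose-versus-placebo comparison for 14.5 points is about 66% with 22 evaluable per group (74% with 26), before any gain from the baseline covariate; 80% power at 22 per group corresponds to about 17 points.

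If the sponsor wants to claim a gain from the covariate, the assumed correlation should be stated with its source. Neither the sample size nor the Tukey procedure has to change. The cost is two sentences and a less favourable stated power.
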